## Abstract

*Background*: Childhood obesity is a critical health issue, both currently and for the foreseeable future. To prevent obesity, behavior changes are essential. Smartphones can be a good tool, as the number of child smartphone users is rapidly increasing. We have developed a mobile platform system named “HAPPY ME,” which is a smartphone application coupled with a wearable device, designed to improve healthy behaviors to prevent childhood obesity. This study aimed to evaluate the effectiveness of obesity prevention among children 10–12 years of age using HAPPY ME. *Methods*: A total of 1000 participants, all fifth and sixth graders from four schools, were assigned to either control or intervention groups by school. Students in the intervention group used HAPPY ME. The study comprises a safety test, a 12-week efficacy test, and a six-month follow-up test to determine the long-term effects of preventive intervention via the integrated service platform. The integrated service platform aims to facilitate child-parent-school participation, involving the child-parent mobile application, a child-teacher mobile web, and a school website. Primary outcome measures are behavioral changes, including healthy eating, increased physical activity, and fitness. Secondary outcome measures are changes in anthropometric parameters (body weight, height, body mass index z-score, and waist circumference), body mass index (BMI) percentiles (obesity rate), and psychological perceptions among participants. *Conclusions*: The results of this study will offer evidence of the effectiveness of a mobile platform service with a multi-component intervention program based on a comprehensive approach.

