
## 2. Methods

### 2.1. Study Participants

Participating schools were recruited by a sanctioned announcement involving official letters from the Metropolitan and Provincial Offices of Education in Gyeonggi Province. Since the recruitment publicity included information regarding the use of mHealth to tackle childhood obesity, the study could not be masked and all applicant schools wished to be designated as intervention schools. We took pragmatic approach to intervention and control group allocation due to the fact schools were unwilling to be randomized. According to our pilot study conducted the previous year, less than 40% of students in fourth grade have smartphones, which can lead to a serious selection bias. The pilot study showed that the number of students who own smartphones increases as students advance through grades at school. Therefore, we determined that fifth and sixth graders were eligible to participate in our research by following a nine-month-long study using smartphones and wearable devices for the prevention of childhood obesity. The sample size was determined based on the government funding, the feasibility of the study, the number of measurements per participant, the number of students we could recruit, and the potential dropout rate considering the age of participants rather than the effect sizes of the intervention. We chose 250 students from each school as an appropriate number, for a total of 1000 students across four participating schools. To categorize children’s weight status, we used the standard growth chart for infants and children by the Korea Centers for Disease Control and Prevention [33]. Written consent was collected from all participating children and their parents. Inclusion criteria were fifth-sixth graders (10–12 years old), no previous diagnosis of systemic or metabolic diseases, and Android smartphone users with parental consent, students who did not refuse to participate (see Figure 1). Finally, 288 students were assigned to a control group, and 558 students were allocated in the intervention group. Any physical restrictions in participants were assessed during meetings with teachers and in loading the program to the smartphone applications of participants.

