#### 2.1.1. Control Group

Students in the control group underwent the same measurements as students in the intervention group, including Physical Activity Promotion System (PAPS) measurements and lifestyle questionnaires administered at the baseline, at week 12, and at month 6. Comprehensive assessments of dietary habits, physical activities, and psychological variables are planned for each assessment period using questionnaires. The control group received the same two group education sessions. Data for these 250 students from one elementary school were collected.

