##### Intervention for Children

Among 750 students from the three intervention schools, students who met inclusion criteria for this study downloaded the “HAPPY ME for students” application. Due to financial and time limits of the developer, the application was developed for Android systems only. This application serves as a self-monitoring tool that focuses on factors known to be associated with childhood obesity including dietary habits, screen time, sleep duration (measured in hours), and physical activity [16,24,25,34,35,36,37,38]. As previously described, HAPPY ME facilitates healthy behavior decisions using gamification and self-monitoring strategies [38,39]. The application sends tailored messages to children to encourage them to complete daily quests for physical activities and to practice healthy dietary habits, such as eating breakfast, choosing fruits and vegetables, and avoiding sugar-sweetened beverages and fast foods, all of which are helpful habits in preventing childhood obesity. The application collects information about participants’ dietary habits and physical performance to categorize and offer optimal feedback to achieve behavioral changes to prevent obesity. Herein, the participating students recorded basic information including weight, height, dietary behavior, and number of hours of sleep at the beginning of the application. Students used height information measured by PAPS at the beginning of the study. Input data in the application automatically categorized the individual status of each student into six categories of dietary behavior and three categories of fitness within the application. For dietary behavior, we defined the following six categories as standard and optimal goals for healthy diets in children: consumption of vegetables five times per day, consumption of fruits twice a day, drinking water instead of sugar-sweetened beverages (SSBs), eating a healthy meal instead of fast or instant food, not eating snacks, and not eating late at night. For physical performance, we defined the following three categories to measure the proper amount of walking per day according to sex: high activity, moderate activity, and low activity. The high activity category includes activities with a number of counted steps over 14,000 steps for boys and over 12,000 steps for girls. Moderate activities are defined as 7000–14,000 steps for boys and 6000–12,000 steps for girls, and low activities are measured as under 7000 steps for boys and under 6000 steps for girls [40]. Once the individual is categorized according to behavior, the application presents a dietary and physical activity quest to encourage users to practice better health behaviors to prevent obesity. Students choose one challenge among the quests presented, and the mission lasts for one week. A tailored message is offered once a day to users based on their performance of the selected quest. After one week, children may choose another quest or continue the previous quest if the quest has not been successfully completed. Eventually, students complete all of the quests according to the guidelines of the application. Participants can monitor their daily and weekly performances, and the application provides feedback and socio-emotionally supportive messages according to user behaviors. These messages are generated from a message pool that the research team developed under a trans-theoretical model. Messages are automatically sent to students according to the logics of each performance. To add a gamification element to the application, children get points if they have completed daily quests, which in turn leads to a higher level of fitness and a healthier diet. Teachers and parents are able to assess how well individuals are doing by comparing these scores among classmates through the application as a series of gamifying elements and, accordingly, to better motivate students to complete the quests assigned to them. If the children do not wish to compare the scores with classmates, they have an option in the application not to be compared. Participants in the intervention group also received an activity tracker called the Walkie + D Coffee (Green Cross Healthcare Inc., Seoul, Korea) via the research team at each school. According to tracker accuracy tests conducted by our developers, the accuracy between volume of oxygen uptake (VO2) and calorie expenditure (kcal/min) through gas analysis and the expenditures of calories according to step count by the device was 80% [41]. Therefore, we considered this device to be a usable activity tracker. Students were instructed to wear the device on their wrist. Daily, weekly, and monthly physical activity data, such as intensity of workouts, step count, and number of calories expended by walking or running with the Walkie + D Coffee, are transferred via Bluetooth to the participant’s smartphone.

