### 2.4. Statistical Analysis

Data is analyzed using statistical software SPSS (version 21.0, IBM Corp., Armonk, NY, USA). Body mass index (BMI) is expressed in percentile according to Korean growth charts [33]. Comparisons of continuous variables between groups within sexes are performed using unpaired *t*-tests or Wilcoxon or Mann-Whitney tests as appropriate, after testing variables for normality of distributions and equality of variances. Comparisons of continuous variables after the trial within groups are performed using paired *t*-tests, Mann-Whitney U tests, or Wilcoxon signed ranks test as appropriate. Chi-square tests or Fisher’s exact probability tests are used to test differences between groups for categorical variables. Comparisons between groups of combined sexes are performed using linear (continuous outcomes) or logistic (categorical outcomes) regressions adjusted for sex, baseline BMI z-score, duration of application usage, and school.

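### The one adjusted between-group regression lists school as a covariate, but school determines group, so its group coefficient has no unique value

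*Protocol article*

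**What the plan says.** The Abstract says that pupils "were assigned to either control or intervention groups by school". Section 2.1 plans 250 pupils per school, "for a total of 1000 students across four participating schools", and then reports enrolment: "288 students were assigned to a control group, and 558 students were allocated in the intervention group".

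Section 2.1.1 places the whole control group in a single school: "Data for these 250 students from one elementary school were collected". Section 2.1.2, under Intervention for Children, gives the other side: "Among 750 students from the three intervention schools".

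Section 2.4 plans two kinds of between-group analysis.

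- Tests without covariates. For continuous outcomes: "Comparisons of continuous variables between groups within sexes are performed using unpaired" t-tests or rank tests. For categorical outcomes: chi-square or Fisher tests.
- One adjusted analysis: "Comparisons between groups of combined sexes are performed using linear (continuous outcomes) or logistic (categorical outcomes) regressions". The same sentence goes on to list the covariates: "regressions adjusted for sex, baseline BMI z-score, duration of application usage, and school".

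No mixed model or random school effect is named. Section 2.2 describes the trial as nonrandomised.

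**The concern.** Every pupil in one school is a control, and every pupil in the other three is in the intervention group. Once school is known, group is known, so a regression that adjusts the group difference for school has nothing left from which to estimate a separate group coefficient.

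This regression is the only adjusted regression that the article specifies, and the trial has no randomisation to fall back on. Fitted as written, software would either omit the group term or drop one school indicator. In the second case the coefficient printed for group is the difference between one intervention school and the control school, and it could be published as the effect of the whole programme.

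**Working it through.** The article gives no alpha, power, effect size or standard deviation, so there is no figure of its own to reproduce. The question is whether the stated model identifies the group coefficient.

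**Inputs.** One control and three intervention schools (sections 2.1.1 and 2.1.2); 288 control and 558 intervention pupils (section 2.1). Assumption: 558 / 3 = 186 pupils in each intervention school, because the split is not given.

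**Step 1: school as a categorical covariate.** Let S1, S2 and S3 indicate the intervention schools. For every pupil, group = S1 + S2 + S3.

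- Intercept + group + S1 + S2 + S3: 5 columns, rank 4.
- Adding sex, baseline BMI z-score and usage duration: 8 columns, rank 7. The R-squared of group on the other covariates is 1.0.
- The rank is the same with the planned sizes (4 x 250). It depends on neither the covariate values nor the outcome.

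**Step 2: what software would print.** Dropping Sk turns the group coefficient into school k minus the control school. One simulated data set with the enrolled sizes (assumed effect 0.3 SD; intervention-school shifts of 0.2, -0.1 and 0.05 SD) gave:

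- drop S1: 0.55
- drop S2: 0.03
- drop S3: 0.26

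These are three parameterisations of the same fit. The average contrast is the same in all of them: (0.545 + 0.031 + 0.256) / 3 = 0.277. A single run contains sampling noise, so it shows the dependence on coding and not its likely size.

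**Step 3: school as a numeric code 1 to 4.** The model has full rank but imposes a linear trend on arbitrary labels. Considering group and the code alone, the variance inflation of the group coefficient is VIF = total variance of the code / its within-group variance. Let p = 558 / 846 = 0.660, so p(1 - p) = 0.2245.

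- Control coded 1 (or 4): between = 0.2245 x 2² = 0.898; within = 0.660 x 0.667 = 0.440; VIF = 1.338 / 0.440 = 3.04.
- Control coded 2 (or 3): between = 0.2245 x (2/3)² = 0.100; within = 0.660 x 1.556 = 1.026; VIF = 1.126 / 1.026 = 1.10.

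**Step 4: would removing school be enough?** Without school, the model has 5 columns and rank 5, so the group coefficient can be estimated. Two problems remain.

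- *Usage duration.* Section 2.2.2 has only the intervention group download the application, so usage is zero for every control. Leaving the other covariates aside, the group coefficient is then (intervention mean - control mean) - b x (mean usage among intervention pupils), where b is the usage slope. That is a difference at zero use, with part of the programme adjusted away.
- *Between-school variation.* For total variance 1 and intraclass correlation r, the variance that pupil-level analysis uses is 1/288 + 1/558 = 0.00526. The true variance is r(1 + 1/3) + (1 - r) x 0.00526. The actual type I error of a nominal 5% test is 2[1 - Φ(1.96 x √(used / true))]. The article gives no r, so a range is assumed:

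| r | actual type I error |
|---|---|
| 0 | 5% |
| 0.005 | 19% |
| 0.01 | 30% |
| 0.02 | 43% |
| 0.05 | 60% |

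A school-level analysis has 4 - 2 = 2 degrees of freedom, with a two-sided 5% critical t of 4.30.

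**The case against.** A reader might infer that the model loses all information about the intervention. It does not. A model with school as a factor estimates each intervention school against the control school, and therefore their average. What is lost is a unique group coefficient, together with any statement of which contrast counts as the intervention effect.

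A reader might also infer that a numeric school code would triple the variance. That holds only if the control school is coded 1 or 4, and the article gives no coding. The range is about 1.1 to 3.0.

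Nor is the regression the only planned step against confounding. Section 2.4 also compares the groups within each sex, and the Discussion presents separate analysis of boys and girls as a control and promises further efforts on confounders and effect modifiers. The accurate statement is that this is the only adjusted regression specified.

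The strongest objection is that section 2.4 does not say how school enters, and a condensed article may leave that to a fuller plan. This stands only in part. The article names ordinary linear and logistic regression and lists the covariates, for which a fixed factor is the natural reading. A fuller plan that followed the list would inherit the aliasing, and one that dropped school would contradict it. A random school effect would make the coefficient estimable, but on about 2 degrees of freedom and still confounded with the one control school.

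**Conclusion.** The point holds. Under the natural reading of section 2.4, group and school are exactly aliased, so the adjusted group coefficient has no unique estimate, whatever the sample size or outcome. This is a stated rule that fails, not a missing detail, and it must be corrected before the adjusted analysis is run.

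The result rests on school being a categorical fixed effect next to a group term. The numeric and random-effect readings allow a fit but do not repair the comparison. The 186-per-school split affects only the variance inflation and type I error figures, and the latter also rest on assumed intraclass correlations. The difference between 250 and 288 control pupils changes nothing. The unadjusted tests can still be computed.

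**What to change.** Rewrite the last sentence of section 2.4.

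1. Do not enter group and school together as fixed effects. Either keep group and drop school, or keep school in place of group and define the intervention effect as the average of the three intervention-school-versus-control contrasts, with all three shown. The second option makes consistency between schools visible.
2. Remove duration of application usage from the between-group model and use it only in an analysis within the intervention group.
3. Adjust for the baseline value of the outcome being analysed.
4. State that the group contrast cannot be separated from the control school's own characteristics.
5. State that pupil-level standard errors and p-values leave out between-school variation, for which there are about 2 degrees of freedom. They are therefore too optimistic, and the comparison should not be presented as a confirmatory test.

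The cost is a few sentences and three contrasts in the output, with no new data. The price is wider stated uncertainty and a weaker conclusion. No change to the model can remove the dependence on a single control school.

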### 2.2. Study Design

The current study is a school-based nonrandomized controlled trial funded by a national grant to prevent childhood obesity in Korea, which has been undertaken utilizing a safety test, a 12-week efficacy test, and a planned subsequent six-month follow-up test for long-term effects. During the study period of 37 weeks, participating students are expected to use their smartphones along with a wearable device, while parents and teachers will receive feedback messages about the performance of participants via smartphones and teacher websites. Data is collected on the part of the research team by monitoring the HAPPY ME platform and spot feedback from teachers and children. For the feedback session with children, our research team will be assigned to each school for three months. A group meeting with parents and teachers for feedback is planned to occur during the three-month efficacy trial. To evaluate the students’ physical performance, data collected by the Physical Activity Promotion System (PAPS) from each school will be monitored. Reporting PAPS data is mandatory in the Korean school system. The PAPS consists of tests to assess cardiac endurance, muscle strength, power, flexibility, and body composition. The PAPS was developed by the Korean government according to public interest in health concerning the growing number of obese and/or weak children. Every elementary school performs PAPS testing once or twice a year to measure student health and, based on results, offers individual exercise prescriptions to every participant. For the schools participating in the application efficacy trial herein, participating students will perform PAPS testing before and after the trial under the guidance of experienced examiners to test the participants’ overall physical fitness, including obesity evaluation, by measuring percent body fat using bioelectrical impedance analysis (BIA). A lifestyle questionnaire which was designed and internally validated was conducted at the beginning of the trial. The questionnaire will also be conducted at week 12 and at the end of the trial. The questionnaire consists of behavioral factors regarding sleep, stress, dietary habits, and activity habits, as well as the amount of screen time by participating children and psychological factors, such as body image. Every participant is required to attend two group education sessions at their respective schools featuring information on a healthy diet and food additives, as well as easy-to-learn physical activities from professionals at week 0 and at week 8 during the 12-week efficacy test period (see Table 1).

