### 2.3. Data Collection

Primary outcome measures are behavioral changes, including healthy eating, increased physical activity according to the application and questionnaire responses, and fitness measurements from the PAPS. Secondary outcome measures are changes in anthropometric parameters (body weight, height, BMI z-scores, obesity prevalence, and waist circumference) based on PAPS, BMI percentile, and psychological variables, such as self-body perception and sleep hours, reported in the questionnaires. Information from PAPS was measured at the time of enrollment, as well as at three months and at nine months following the trial.

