There are some limitations that need to be addressed. First, the current trial was not randomized or blind controlled. School involvement is one of the most important aspects of the trial—as school motivates children—but schools are the most difficult group to recruit for randomized controlled trials (RCTs), especially when smartphones are involved. Schools do not allow random allocation. The participating schools herein agreed to join this project only once they were apprised of the allocation of students, as well as all process and content provided to the children. Most of the schools wanted to be involved in the intervention group. Blinding was also impossible for the intervention and control groups, which may have added bias to the results. During our forthcoming analysis, we will try to control related factors as confounders and effect modifiers. In addition, we will try to identify the difference between users and non-users following the trial, beyond only the intervention and control groups. Secondly, the duration of the trial is less than a year, whereas obesity prevention studies recommend longer durations [11,12]. Therefore, we could not use obesity prevalence or BMI z-scores as primary outcomes. Nevertheless, behavior changes are the most important outcomes in achieving a healthy weight in the long term. Thirdly, students who owned smartphones with Android operating systems were able to join the study in the intervention group. More than 90% of fifth-sixth graders possess smartphones, and more than 95% of them have Android systems. Finally, we could not develop gender-specific programs, even though it is known that boys tend to be more obese than girls [1,2,36]. Sugar intake also varies by sex [33]. Separate analysis in boys and girls would control those confounders, however, making clear which factors are more related to gender in childhood obesity. Future trials to develop and assess the effects of gender-specific programs for long-term prevention of childhood obesity, together with the integration of schools, are needed. Because there is evidence that low socioeconomic status and low fruit and vegetable intakes are associated with obesity, it would be more effective if future studies were able to target specific gender and socioeconomic samples for intervention [16,25]. The results of this study will offer evidence of the effectiveness of a multi-component prevention program that involves both schools and parents together with the use of smartphones and wearable devices.

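### The between-group regressions adjust for neither age nor grade, although schools were allocated without randomisation and some outcomes are raw growth measures

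*Protocol article*

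**What the plan says.** Section 2.4 gives two kinds of between-group comparison. For the sexes combined, it specifies "regressions adjusted for sex, baseline BMI z-score, duration of application usage, and school". Within each sex there is no model: "Comparisons of continuous variables between groups within sexes are performed using unpaired" t-tests or rank tests, and no covariates are named. The only measure that 2.4 refers to a growth chart is BMI.

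Section 2.3 lists as secondary outcomes "changes in anthropometric parameters (body weight, height, BMI z-scores, obesity prevalence, and waist circumference) based on PAPS". PAPS fitness is part of the primary outcome; its scale is not stated.

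On allocation, the Abstract says that participants "were assigned to either control or intervention groups by school", and section 2.1 says: "We took pragmatic approach to intervention and control group allocation due to the fact schools were unwilling to be randomized". There are three intervention schools and one control school. Pupils are in grades five and six, aged 10 to 12. No matching, stratification or balancing on grade is described.

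Two statements bear on the grade mix. Section 2.1 reports from the pilot that "the number of students who own smartphones increases as students advance through grades at school". The Discussion says: "More than 90% of fifth-sixth graders possess smartphones, and more than 95% of them have Android systems". The Discussion also undertakes to deal with confounders in the analysis, but names no variable.

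**The concern.** Covariate adjustment is the only protection against a grade imbalance in this design, and the stated covariates do not provide it.

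- A BMI z-score at baseline is already standardised for age, so it carries little information about age.
- School does not stand in for grade among pupils. School also determines group, so a fixed school effect competes with the group effect and cannot be relied on to adjust for anything between arms.
- The within-sex tests adjust for nothing.

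Because the outcomes are changes, the plain difference in size between grades largely cancels. What can remain is a difference in the rate of growth, since children of 10 to 12 years may grow at different rates over nine months. If one arm holds more sixth graders, part of the group difference in change in weight, height or waist is then growth and not intervention. The same holds for PAPS fitness if it is analysed on a raw scale.

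**Working it through.** The documents give no grade mix and no growth difference by grade, so there is no stated figure to reproduce. The size has to be bounded under stated assumptions.

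**Inputs from the article.** Arms of 558 and 288 (section 2.1); smartphone ownership of 90% in grades five and six, the floor given in the Discussion; three intervention schools and one control school.

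**Assumptions.** Equal grade sizes; the same Android share in both grades; no phone filter in the control school; a difference between grades in mean change of 0.1 to 0.5 SD of change.

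**Step 1: largest grade shift through phone ownership.** If ownership averages 90%, the widest possible gap is 100% in grade six against 80% in grade five. The sixth-grade share of owners is 1.00/(1.00 + 0.80) = 0.556. The excess over 0.50 in an unfiltered control school is 0.056.

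**Step 2: bias.** Bias = excess share × difference between grades, so 0.0556 × 0.1 = 0.006 SD up to 0.0556 × 0.5 = 0.028 SD.

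**Step 3: false-positive rate.** SE = √(1/558 + 1/288) = 0.0726 SD, ignoring clustering. Error = P(|Z + bias/SE| > 1.96).

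| Difference between grades (SD) | Bias (SD) | Error of a nominal 5% test |
|---|---|---|
| 0.1 | 0.006 | 5.1% |
| 0.2 | 0.011 | 5.3% |
| 0.3 | 0.017 | 5.6% |
| 0.5 | 0.028 | 6.7% |

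Within one sex, taking half of each arm (279 v 144), SE = √(1/279 + 1/144) = 0.1026, and the error at a bias of 0.028 SD is 5.8%.

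**Step 4: sensitivity to the ownership figure.** The pilot figures are lower: 55.2% across grades four to six (Introduction) and under 40% in grade four (section 2.1). If both describe the same pupils, a straight-line rise from 40% gives 55.2% in grade five and 70.4% in grade six. The sixth-grade share is then 70.4/(55.2 + 70.4) = 0.561, an excess of 0.061, and the bias at 0.5 SD is 0.030 SD. This is the same order as in Step 2, and somewhat more if grade four lay well below 40%.

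**Step 5: if schools differ in grade mix for other reasons.** A gap of 20 percentage points, which is purely an assumption, gives a bias of 0.20 × 0.2 = 0.04 SD to 0.20 × 0.5 = 0.10 SD, and an error of 8.5% to 28%. A simulation of 2,000 trials used shares of 60% v 40%, a difference between grades of 0.5 units and an SD of 1.5 units. It gave a bias of 0.10 units and an error of about 15% without grade, and a bias of about 0 and an error of about 4% with grade in the model. It left out the school and usage terms.

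**Step 6: comparison with clustering.** With 3 v 1 schools and an assumed intraclass correlation of 0.01, the true SE is √(0.01 × (1/3 + 1) + 0.99 × (1/558 + 1/288)) = 0.136. A child-level test then has an error of 29.6% with no age bias and 30.6% with a bias of 0.028 SD.

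**The case against.** The case against acting is substantial. No grade imbalance is shown: both grades were targeted in every school, and the age range is narrow. The only mechanism found in the article gives a small bias. If the Android criterion also applied in the control school, it gives about none. Section 2.1 states that criterion without splitting it by arm; the Discussion ties it to the intervention group, so the point is open. The larger error rates need a 20-point gap that nothing in the article supports. The outcomes certainly exposed are secondary, and the obesity measures themselves are not exposed in this way. With one control school and a school term, the combined-sex model does not identify the group effect (intercept, group and three school indicators make five columns of rank four), so adding age alone gives no valid estimate from it. Finally, this is a condensed article, and the Discussion signals that confounders will be handled.

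Most of this stands as a limit on the size of the problem. It does not remove the point. Section 2.4 names its covariates explicitly, so this is a stated choice and not a detail left to an unseen analysis plan. The Discussion's undertaking names no age term and does not change the list. The group-by-school aliasing needs its own repair, but repairing it would not remove a difference due to age. The within-sex comparisons contain no school term, so age adjustment works there directly.

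**Conclusion.** The point holds as a risk. The adjustment set omits age and grade in a non-randomised, school-allocated study of growing children, and nothing else in the design handles age. The likely bias is small: about 0.006 to 0.03 SD of change through phone ownership, given a difference between grades of 0.1 to 0.5 SD and no phone filter in the control school. It would be larger only if the schools differ in grade mix for other reasons, which the article does not show. It is minor beside clustering and the aliasing of group with school. The change should be made because it removes a possible confounder at almost no cost, and because naming the term beforehand avoids a later choice of adjustment made with the results in view. Confidence is medium, since the grade mix and the growth difference are both assumed.

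**What to change.** In section 2.4, add age at measurement (or grade) to the covariates of every between-group regression. For the within-sex comparisons, report the same age-adjusted regression in each sex beside the two-sample tests. Optionally, also report weight and height as age- and sex-specific z-scores.

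The cost is one sentence and one degree of freedom. Age must already be held to compute BMI percentiles, so no new data are needed.
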